### Clinic eligibility and recruitment

Any clinic in Oregon providing primary care to adult patients is eligible for the study. Prior work by our team identified approximately 750 primary care clinics in Oregon that meet eligibility criteria; we aim to engage approximately 20% of potentially eligible sites [35]. ANTECEDENT uses a rolling recruitment process to capitalize on changing capacity and interest in clinics, health systems, and CCOs over time. Clinic recruitment begins with engagement and outreach to regional CCOs and clinics with established ORPRN relationships. Prior research in Oregon suggests that larger and system-affiliated clinics are prioritized for support by the CCOs [36]. Thus, recruitment activities focus on reaching small- to medium-sized clinics (defined as clinics with fewer than 10 primary care providers) and independent clinics.

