#### Clinic contact logs

Following all clinic interactions, practice facilitators will record field notes in REDCap using structured forms containing open- and closed-ended prompts. Practice facilitators will use two types of structured note-reporting guides to record their interactions and clinic support. Brief communication logs will track short interactions with clinics (e.g., email outreach, scheduling), and in-depth intervention tracker forms will describe engagement, content, and the quality of scheduled facilitation meetings. The logs will produce evaluation data specified in the request for applications, such as the number and type of interactions and implementation strategies employed. The intervention tracker documents practice facilitator tailoring concerning clinic context and perceptions of clinic capacity for change. A qualitative analyst will regularly review the clinic contact logs for completeness.

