#### Exit assessment

All clinics will participate in an exit consultation, coordinated by the practice facilitator, in the final quarter of the intervention (months 13–15). The closing activities allow solidifying program maintenance and updating the clinic intake form (including the SBIRT and MAUD implementation checklist). During the exit assessment, we will also collect the second set of SBIRT and MAUD performance data to compare SBIRT and MAUD delivery rates to eligible patients at baseline and post-intervention per the specifications of the request for applications and external evaluation. We anticipate that some clinics will develop the capacity for baseline reporting via participation in the intervention. After completing these activities, the practice facilitator will connect the clinic point of contact to the qualitative team to complete the study exit interview. Additional information on the clinic intake form (baseline assessment) and exit interview (key informant interviews) are provided above and in Table 4.

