### Data analysis

#### Quantitative analytic plan

Quantitative data will be analyzed using Stata. We propose two primary performance outcomes. The first is the difference between baseline and exit assessment in the percentage of eligible patients who receive screening for UAU (and drug risk when using Oregon’s SBIRT protocol), brief intervention, and MAUD. Because baseline levels may be strongly correlated with change, we also plan to conduct a sensitivity analysis to scale the change as a proportion of the initial gap between baseline and target. The second outcome is whether the clinic can report the Oregon CCO SBIRT metric to its regional CCO by the end of the study. These outcomes will serve as the dependent variable of a linear (percentage difference) or logistic (ability to report CCO measure) regression model.

To evaluate the impact of tailored implementation support on SBIRT, MAUD, and QI capacity (Aim 2), we will combine data on clinics’ previous collaborations with ORPRN, how clinics were referred to ANTECEDENT and the number and types of contacts in the recruitment and implementation phases. We will use logistic regression to determine which factors increase the probability of successful recruitment and project completion. In addition to the predictors above, we will account for the possibility that the level of implementation success depends on the specific practice facilitator or CCO. We anticipate that higher-intensity contact will be negatively associated with clinic enrollment but positively associated with study completion (defined as participation in exit assessment). We further hypothesize that implementation support will be most effective when clinics have a QI lead and clinic champion.

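### The completion model predicts exit-assessment participation from a contact count that grows with time enrolled, which biases it towards the anticipated positive association

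*Protocol article*

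**What the plan says.** All of this comes from the protocol article.

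- **Predictor.** For Aim 2, the Quantitative analytic plan combines prior collaboration and referral route with "the number and types of contacts in the recruitment and implementation phases". It names no common time window, rate per month or landmark. Higher intensity is not defined, and number and types are the only contact measures named.
- **Model and purpose.** "We will use logistic regression to determine which factors increase the probability of successful recruitment and project completion".
- **Outcome and expected sign.** Completion is defined and both signs are stated in one sentence: "We anticipate that higher-intensity contact will be negatively associated with clinic enrollment but positively associated with study completion (defined as participation in exit assessment").
- **When completion is decided.** The Exit assessment section describes a consultation "coordinated by the practice facilitator, in the final quarter of the intervention (months 13–15").
- **How contacts accrue.** Under Clinic contact logs: "Following all clinic interactions, practice facilitators will record field notes in REDCap". Short exchanges, including scheduling, go in brief communication logs. Scheduled facilitation meetings go in a separate intervention tracker.
- **Numbers.** Sample size considerations gives 150 clinics recruited, 20% attrition and 120 retained.

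**The concern.** The predictor is measured over the same period that decides the outcome. A clinic that leaves in month 4 has about four months of logged contacts; one that reaches the exit assessment has a year or more. Even if contact did nothing for retention, completers would show higher counts because they were there longer. This is the familiar immortal-time problem. Logs about arranging or holding the exit assessment add to it, because those contacts exist partly because the clinic completed.

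The plan then reads the coefficient as showing which factors raise the probability of completion, with a positive sign stated in advance, and the bias runs in that direction. The study could credit contact intensity with retention when retention produced the contacts. That would mislead programmes deciding how much facilitator time to fund.

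The enrolment model has a related weakness. Total outreach contacts depend on when outreach stops, and that depends on the clinic's answer.

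**Working it through.** **The plan's own figures.** 150 × (1 − 0.20) = 120 retained, so 30 non-completers; 750 × 0.20 = 150 recruited. Both reproduce. The protocol states no alpha, power or effect size for the contact models.

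**Expected counts when contact has no effect.** Let a clinic log r contacts per month until month 12 or dropout. A completer expects 12r. A non-completer expects r × (mean months enrolled).

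- Dropout uniform over months 0–12: mean stay 6 months, so 12r against 6r, a ratio of 2.
- Dropout uniform over months 6–12: mean stay 9 months, so 12r against 9r, a ratio of 1.33.
- Dropout uniform over months 9–12: mean stay 10.5 months, so 12r against 10.5r, a ratio of 1.14.
- Non-completers stay to month 12 and miss only the exit assessment: ratio 1.

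**Null simulation, completion.** From the protocol: 150 clinics, 20% attrition. Assumed: 0.5–2 contacts per month, between-clinic coefficient of variation (CV) 0.3–1.0 (gamma rates, Poisson counts), accrual over 12 months, dropout independent of contact, two-sided 5% level. Each scenario had 1,000 runs, with a logistic regression of completion on the cumulative count.

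| Scenario | Significant and positive |
|---|---|
| Dropout over months 0–12, CV 0.3 | 100% |
| Same, CV 0.6 | 96–98% |
| Same, CV 1.0 | 71–76% |
| Months 0–12, 1/month, CV 0.6, 10% attrition | 85% |
| Same, 20% attrition, 25% or 50% of clinics foundational-only | 87% or 65% |
| Same, recruitment contacts added to the count | 97% |
| Dropout over months 6–12, 1/month, CV 0.6 | 42% (about 51% in a second run of this check) |
| Dropout over months 9–12, 1/month, CV 0.6 | 13% (14% in the second run) |
| Miss only the exit assessment | 2.2% (4.6% significant in either direction) |

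The spurious effect can be large. At 2 contacts per month and CV 0.3, the median odds ratio was 1.206 per contact, or 1.206^10 ≈ 6.5 per 10 contacts. At CV 0.6 it was 1.09^10 ≈ 2.4.

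**Exit-related logs.** The table counts none. If completers log on average 2–4 more exit contacts than non-completers (assumed; 500 runs; 1–2 contacts per month, CV 0.3–0.6), false positives where clinics miss only the exit assessment rise from 4–6% to 8–95%. For dropout in months 9–12 they rise from 14–38% to 35–100%. Failed scheduling attempts with non-completers would narrow that gap.

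**Alternatives under the null.** A discrete-time model using the prior month's contacts gave roughly 4–9% significant results. Contacts in months 1–3 among clinics still enrolled at month 3 gave 4.6%, and contacts per month enrolled gave 6.5% (both at 1/month, CV 0.6).

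**Null simulation, enrolment.** 750 clinics, 20% enrolling with the answer fixed in advance, at most 8 contacts, 500 runs, Welch test of counts by enrolment; the stopping patterns are assumed.

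- Non-enrollers pursued longer (3.2 against 5.7 contacts, enrollers first): significant negative in 100% of runs.
- Refusers dropped sooner (4.2 against 2.5): significant positive in 100%.
- Equal stopping: 2.0% negative plus 3.4% positive, about 5%.

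**The case against.** **The result is not automatic.** This stands. The table shows how strongly the false-positive rate depends on dropout timing, which the protocol does not give. The accrual period matters too: support is described as lasting 12 months (Abstract), 9 months (Supplemental implementation support plan) and six months (practice facilitation row, Table 3). With accrual in months 3–9 only, 2 contacts per month and CV 0.6 (all assumed), the null gave 84% for dropout over months 0–15, about 6% for months 6–15 and about 3% for months 9–15. At 1 contact per month and CV 1.0, with dropout over months 0–15, it gave 45%.

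**Intensity could mean a rate, and an analysis plan not shown may define it so.** Possible, but the article names the number of contacts, the model, the outcome and the sign, and that combination is biased as written. The separate log types make exit scheduling easier to isolate, but nothing says it will be excluded.

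**The model is secondary.** This also stands. The two primary outcomes are change in performance and ability to report the CCO metric; neither uses this model, and the contact expectation is worded as an association.

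**Two stronger readings are not supported.** A reader might infer that the negative enrolment sign is likewise guaranteed. The protocol does not say when outreach stops, and one plausible rule gives the opposite sign. A reader might also infer, from "Clinic recruitment begins with engagement and outreach to regional CCOs and clinics with established ORPRN relationships", that Hypothesis 2a is favoured because clinics with prior ties have longer to enrol. But outreach starts with CCOs as well, so the warm-handoff route also starts early. Recruitment is rolling with no stated cut-off, and the hypothesis concerns engaging with and completing all study elements, not enrolment alone.

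**Conclusion.** The concern holds for the completion model. A cumulative implementation-phase count is partly a consequence of staying enrolled, and the bias favours the anticipated sign whenever non-completers leave while contacts are still accruing. Under 12-month accrual with all clinics contacted and 20% attrition, the chance of a spurious positive finding is about 70–100% for dropout spread over the year, about 40–50% for months 6–12, about 14% for months 9–12, and nominal if only the exit assessment is missed and exit logs are not counted. These figures rest on assumed contact rates, spread and timing; shorter accrual or many foundational-only clinics lowers them.

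For enrolment, the count reflects the outreach stopping rule, but the direction cannot be known from the document. The completion and enrolment definitions should be corrected before analysis. This does not threaten the primary outcomes.

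**What to change.** - **Completion, preferred.** Replace the cumulative count with a discrete-time (monthly) model of dropout, using the prior month's contacts among clinics still enrolled.
- **Completion, alternative.** Use recruitment-phase contacts plus contacts in a fixed window that extends into the implementation period, among clinics still enrolled when it closes. A window of months 1–3 alone controls the error rate but misses the question: those months are the baseline assessment given to every clinic (Foundational support; Table 4, footnote a), before most implementation contact.
- **Exit-related logs.** Exclude logs about arranging or conducting the exit assessment.
- **Enrolment.** Count contacts within a fixed window from first approach.
- **Wording.** Report associations, not factors that raise the probability. Even prior-month contacts may fall because a clinic is already withdrawing.

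The cost is analysis wording and some data preparation on logs that are filed after each interaction anyway; no new data are needed. With the window alternative, clinics lost before it closes must be described separately.

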#### Qualitative analytic plan

All qualitative data will be maintained in ATLAS.ti and analyzed to identify patterns or themes according to Miller and Crabtree’s editing method [52, 53]. Our theoretical framework, a hybrid of i-PARIHS [33] and DSF [34] (Fig 1), will inform coding and analysis. Transcripts from the interviews with CCO staff will be coded and analyzed concurrently with data collection to identify how CCOs support clinics in achieving the SBIRT quality incentive metric (Aim 1). The remaining qualitative data (interviews with clinic contacts and PERCs, clinic contact logs, clinic surveys, baseline assessment, and periodic reflection transcripts) will be coded and analyzed on a rolling basis as clinics conclude participation in the intervention. Multiple coders will analyze, discuss data, and synthesize findings of clinic context, QI capacity, engagement with the intervention, level of implementation support provided, clinic disruptions, and ability to capture and report quantitative performance data on SBIRT and MAUD. In addition to clinic-level analysis, qualitative data about practice facilitator expertise and perspectives of practice transformation will be analyzed concerning study Aim 3. Preliminary themes at both levels will be identified and refined in consultation with the study team and ANTECEDENT Advisory Board as a form of member checking [52, 53].

#### Systems science analytic plan

To examine how practice facilitators tailor implementation support based on clinic context, the SBIRT innovation, and expertise over time, we will systematically generate causal-loop diagrams from qualitative data to describe changes in practice facilitators’ perspectives of practice transformation (Aim 3). Causal-loop diagramming is a method from systems science that identifies feedback loops driving nonlinear behavior in complex systems [54, 55]. Diagrams corresponding to each facilitator’s perspective will allow for comparison between individuals over time. Once data collection is complete, we will use a group modeling approach [56] to synthesize the team’s mental model of effective practice transformation to support SBIRT and MAUD in primary care.

#### Mixed-methods convergence

Finally, we will merge our quantitative, qualitative, and systems science data using joint displays to reconcile differences and enable the identification of patterns and themes across clinics [57]. To further examine implementation support provided to clinics (Aim 2), we will review descriptive statistics from the clinic contact logs, clinic intake form, and HIT capacity assessment in tandem with our qualitative data. Our goal is to classify clinics along three primary dimensions: (1) baseline capacity, (2) level of implementation support, and (3) observed improvement, and to examine details of the relationships among them. To define baseline capacity, we will categorize clinics as “high”, “medium”, or “low” based on QI infrastructure and workflows for SBIRT and MAUD during the baseline assessment. Qualitative and quantitative analysts will conduct a card sorting activity to classify the participating clinics based on the level of implementation needed to implement SBIRT and MAUD successfully. Analysts will use these resulting categories to create causal predictive matrices to describe clinic features and understand the factors associated with improvement [58]. We will use correspondence analysis to investigate relationships between categorical variables (for example, whether the distribution of implementation support activities varies with clinic baseline capacity) and latent class analysis to identify groups of clinics with similar characteristics. These methods represent high-dimensional data in a low-dimensional space so that it is easier to identify patterns and critical features [59]. We hypothesize that depending on the clinic context, varying levels of implementation support may be needed to support “successful implementation”. We will strive to identify case examples to inform studies using predictive models for tailored implementation support.

#### Sample size considerations

Recruiting 150 clinics will ensure we retain a minimum of 120 clinics in the final analysis after an anticipated attrition rate of 20% based on prior studies. While we lack preliminary performance estimates for SBIRT for UAU to inform power calculations, for a similar measure—depression screening and follow-up—the OHA reported that CCO performance in the first year of tracking (2014) ranged from 3.3% to 68.1% [60]. Thus, we anticipate similar, significant variability in clinic-level performance outcomes. Our sample of 120–150 clinics ensures that even targeted sub-group analyses performed at the clinic level will have desirable “large” sample properties [59].

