### Study leadership and setting

ANTECEDENT is a partnership between the Oregon Rural Practice-based Research Network (ORPRN), SBIRT Oregon, and the Oregon Health Authority (OHA) Transformation Center. ORPRN is a practice-based research network (PBRN) established in 2002 with a mission to “improve health outcomes, and equity for all Oregonians through community partnered dialogue, research, coaching and education” [18, 22, 23]. PBRNs play an important role in the United States and internationally in bridging research discoveries and routine practice [24, 25]. ORPRN leverages statewide relationships with clinic and community partners, regionally distributed practice facilitators, and a mixed-methods evaluation team to support study activities. SBIRT Oregon (www.sbirtoregon.org) is an established online toolkit designed to support training and implementation of the SBIRT process in clinical practice. The website includes multiple tools and resources (e.g., demonstration videos, clinical workflow guides) to increase SBIRT and MAUD and empower clinicians in primary care to act on positive screening for unhealthy substance use [12]. The OHA Transformation Center oversees many aspects of the implementation and evaluation of Oregon’s regional Medicaid Coordinated Care Organizations (CCOs) and provides technical assistance to support transformation efforts [26]. OHA introduced SBIRT for unhealthy alcohol and drug use as an annual quality metric for Oregon CCOs in 2013; the SBIRT metric has been reported in multiple years since (S1 Appendix) [27]. ANTECEDENT study activities were designed to align with the CCO SBIRT quality incentive metric in collaboration with OHA and the 15 CCOs operating in Oregon at grant submission [28].

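### At 20% attrition, 120 retained clinics is the expected number and not an ensured minimum, and the large-sample assurance for subgroups has no subgroup sizes behind it

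*Protocol article*

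**What the plan says.** Under Sample size considerations, the protocol article makes two assurances. The first concerns retention: "Recruiting 150 clinics will ensure we retain a minimum of 120 clinics in the final analysis after an anticipated attrition rate of 20" per cent. The second concerns subgroups: "Our sample of 120–150 clinics ensures that even targeted sub-group analyses performed at the clinic level will have desirable “large” sample properties". Between them it concedes that "we lack preliminary performance estimates for SBIRT for UAU to inform power calculations", so no power calculation is offered.

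The Quantitative analytic plan sets out what these clinics must support:
- a linear model for the change from baseline to exit in the percentage of eligible patients served;
- a logistic model for whether the clinic can report the CCO metric;
- logistic models for recruitment and for completion, where completion means taking part in the exit assessment.

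The listed predictors for recruitment and completion are previous collaboration with the network, referral route, and the number and types of contacts. The plan also allows that implementation success "depends on the specific practice facilitator or CCO". Mixed-methods convergence sorts clinics into three tiers of baseline capacity, and Study leadership and setting gives 15 CCOs.

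**The concern.** An anticipated attrition rate yields an average. Calling that average a minimum tells the reader that the risk of ending below 120 has been dealt with, when on the stated rate it is close to an even chance.

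The attrition allowance also covers only clinics that leave. The change outcome can lose further clinics that stay but lack usable performance data at one of the two times. The Exit assessment section itself expects some clinics to acquire the capacity for baseline reporting only by taking part.

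The subgroup sentence moves from the size of the whole sample to the behaviour of its parts without saying how large the parts are. A reader could take subgroup and completion-model estimates as more dependable than the numbers allow.

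**Working it through.** **Inputs from the protocol article.** 150 clinics recruited, 20% attrition, minimum of 120, 120–150 clinics for analysis (Sample size considerations); 15 CCOs (Study leadership and setting); three capacity tiers (Mixed-methods convergence); completion defined by the exit assessment (Quantitative analytic plan).

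**1. The plan's own figure.** 150 × (1 − 0.20) = 120, and 120 / 0.80 = 150. Both reproduce exactly.

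**2. Is 120 a minimum?** Take the number retained, X, as Binomial(150, 0.80), assuming independent losses.
- Mean 120; SD = √(150 × 0.8 × 0.2) = 4.9.
- P(X ≥ 120) = 0.55.
- 5th percentile 112, with P(X ≥ 112) = 0.955; central 95% range 110–129.
- To have a 95% chance of at least 120 at this rate, about 160 clinics would be recruited (158 for 90%).

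The result depends on the true retention rate:

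| True retention | P(at least 120 of 150) |
|---|---|
| 75% | 0.09 |
| 78% | 0.32 |
| 80% | 0.55 |
| 82% | 0.77 |
| 85% | 0.96 |

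**3. Change outcome.** Let *u* be the share of retained clinics with usable data at both baseline and exit. The article does not give it, so I assume 0.9, 0.8 and 0.7. The expected number analysed is 120 × *u* = 108, 96 and 84.

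**4. Subgroup sizes, if clinics were spread equally.**
- Tiers: 120/3 = 40 to 150/3 = 50.
- CCOs: 120/15 = 8 to 150/15 = 10.

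As a guide to precision, the 95% half-width for a proportion of 0.5 is 1.96 × √(0.25/*n*):

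| Group | *n* | Half-width (percentage points) |
|---|---|---|
| Whole sample | 120–150 | 9–8 |
| One tier | 40–50 | 15–14 |
| One CCO | 8–10 | 35–31 |

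**5. Completion model.** Expected non-completers = 150 × 0.20 = 30. If CCO entered as 14 indicators, that alone would leave 30/14 = 2.1 non-completers per parameter, before any named predictor. Under a guide of 10 events per parameter (my assumption), 30 events carry about 3 parameters.

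**The case against.** The strongest reply is that this is loose wording around correct arithmetic. The 20% is said to come from prior studies and may be cautious; if true retention were 85%, the chance of at least 120 would be 0.96. That stands as a caveat on the 0.55, but the article presents 20% as what it anticipates, and on that figure the assurance fails.

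A shortfall in performance data is possible but not shown. The article provides for manual tracking and chart audit, and clinics that gain reporting capacity later may recover their baseline figures. So the change outcome *may*, not *must*, have fewer than 120.

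Large-sample properties can also mean asymptotic behaviour rather than power, and the article claims no subgroup power. Even so, 8–10 clinics per CCO is not large in that sense, and 40–50 per tier is doubtful once a tier is split further.

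Several stronger readings are tempting but not supported:
- *The planned models in general are too small.* The linear model on 120 or so clinics is adequate for a few predictors. The recruitment model could draw on the roughly 750 eligible clinics.
- *The completion model will certainly suffer separation.* The article does not say whether facilitator or CCO is a fixed or a random effect, a choice often left to the analysis plan, and it does not give the number of facilitators.
- *The article contradicts itself on available data*, because "the SBIRT metric has been reported in multiple years since". That metric covers alcohol and drugs and is set for CCOs, whereas the missing estimates are for SBIRT for unhealthy alcohol use. No contradiction is established.
- *The depression-screening range is a faulty power input.* The statement that "CCO performance in the first year of tracking (2014) ranged from 3.3% to 68.1" per cent is used only to anticipate wide variability. If clinics vary more than CCOs do, that conclusion is strengthened. For the same reason, detectable differences in percentage points cannot be derived from it without outside assumptions.

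**Conclusion.** The point holds as an overstatement in two sentences, with a consequence for one model.

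- **Retention.** 120 is the expected number. The chance of reaching it is about 0.55, and 112 or more is the figure with about 95% probability. Both rest on a true rate of exactly 20% and independent losses.
- **Subgroups.** The assurance is unsupported, since no sizes are given and the article's own groupings average 40–50 and 8–10 clinics, assuming equal spread.
- **Completion model.** About 30 non-completers are few for prior collaboration, referral route, contacts, and facilitator or CCO. How serious this is depends on how those last two are entered.

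The whole-sample linear analysis is not put in doubt.

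**What to change.** 1. Replace the retention sentence with: 150 clinics are expected to yield about 120 (112 or more with about 95% probability if losses are independent).
2. State separately how many clinics are expected to have usable performance data at both baseline and exit, and use that number for the change outcome.
3. Replace the subgroup assurance with expected subgroup sizes and their precision, or label the subgroup analyses exploratory.
4. In the completion model, enter facilitator and CCO as random intercepts, or use penalised likelihood, and keep the fixed predictors few.

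The cost is wording and model specification. No clinics or data collection are added, but the stated figures become less favourable.
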